### Sample size

The sample size in qualitative research is driven by data saturation. However, there are no standard criteria for calculating the sample size for this type of study. Blome et al. (9) set their sample size in the process guided by information power. We assume the sample size should be large enough to reveal at least *n* = 20 patients with health state fluctuations. Sun et al. (2) examined a sample size of *n* = 55 patients and found significant associations regarding fluctuations in HRQoL. However, the percentage of patients with dementia reporting health state fluctuations within 14 days is currently unknown. We, therefore, hypothesize that a sample size of *n* = 50 patient and caregiver dyads would be large enough to bear HRQoL outcomes (see health fluctuation outcomes below) and achieve the aims of this study.

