### Data collection

At baseline, day seven and day 14, the EQ-5D-5L (13, 14) will be administered *via* standardized face-to-face interviews by dementia-specific qualified nurses at patients' or caregivers' homes. Both patients (self-rating) and caregivers (proxy-rating) will be asked to complete the EQ-5D-5L (in separate rooms). Also, patients' socio-demographic (age, sex, living situation) and the following clinical data will be assessed at baseline: cognitive impairment according to the Mini-Mental State Examination (MMSE) (15, 16), depression according to the Geriatric Depression Scale (17), perceived social support according to the F-SozU (18), deficits in daily living activities according to the Bayer Activities of Daily Living Scale (19), and comorbidity according to the Charlson Comorbidity Index (20, 21). A brief description of the assessed clinical outcome measures is demonstrated in the section “measures.”

After completing the baseline assessment, caregivers will daily self-complete a fluctuation diary for 14 days, documenting the frequency and intensity of health state fluctuations, affected dimensions, and underlying health events (see Figure 2). After completing the fluctuation diary, the diary data will be collected, and the study nurse will conduct a semi-structured interview on day 14 about the documented recurrent health state fluctuations, the possible consideration of these fluctuations in the assessment of health today using the EQ-5D-5L, and appropriate recall periods to capture recurrent fluctuations of HRQoL more accurately in dementia. The questions of the semi-structured interview are displayed in Table 1. Furthermore, guidelines will be drafted, and the nurses will be trained to ensure the replicability of interviews and promote data quality.

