To assess the association between occurrence, frequency and intensity of the reported health fluctuation and (i) the differences between the baseline, 7-day and 14-days follow-up EQ-5D-5L profile, health utility and EQ-VAS as well as the (ii) reporting of consideration of these health state fluctuations in the assessment of health today in the EQ-5D-5L, we will use appropriate statistics such as cross tables with ANOVA, *t*-tests and multiple logistic regression models. According to the latter one, multivariate regression models will include the adherence to the recall period (dichotomous: yes, no) as a dependent variable and the fluctuation intensity (low, moderate, high) and further socio-demographic and clinical variables of the patient as an independent variable. We hypothesize that frequent and more intensive health fluctuations reported in the diaries will cause higher variability of the EQ-5D-5L index between baseline and seven or 14 days later and will have higher odds for consideration of these fluctuations in the assessment of HRQoL today (non-adherence to the recall period of today). Additionally, we will use descriptive statistics to identify specific health events most likely affecting the incorporation into the health assessment today. Statistical analysis will be carried out in SAS (version 9.4 M7).

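### The adherence regression sets an open-ended covariate list against at most 25 dyads in the smaller outcome class; it needs penalised estimation, few terms and a more modest sample-size claim

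*Protocol article*

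**What the plan says.** Under Quantitative data preparation and analyses, the protocol article commits to multiple logistic regression with "the adherence to the recall period (dichotomous: yes, no) as a dependent variable". The independent variables are "the fluctuation intensity (low, moderate, high) and further socio-demographic and clinical variables of the patient as an independent variable". The same paragraph attaches a directional hypothesis: more frequent and more intense fluctuation should raise the odds that past fluctuations enter the rating of health today.

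The covariates are not listed there. Data collection gives the pool: "socio-demographic (age, sex, living situation) and the following clinical data will be assessed at baseline", followed by MMSE, Geriatric Depression Scale, F-SozU, Bayer ADL scale and Charlson index. That is three socio-demographic and five clinical variables.

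Sample size states that "there are no standard criteria for calculating the sample size for this type of study". It refers to saturation, to information power in a comparable study and to an earlier study of 55 patients, and asks for at least "20 patients with health state fluctuations". It concedes that "the percentage of patients with dementia reporting health state fluctuations within 14 days is currently unknown". It then concludes that 50 dyads would be "large enough to bear HRQoL outcomes (see health fluctuation outcomes below) and achieve the aims of this study". The regression is not mentioned in that argument.

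**The concern.** A logistic model draws its information from the smaller of the two outcome classes, not from the total sample. In 50 dyads that class is small whatever the result, and the plan spends two parameters on intensity before any covariate enters. With few events per parameter, unpenalised maximum likelihood pushes odds ratios away from 1, sometimes to extreme values, and some samples give no finite estimate.

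The model carries some weight. It is the test of the stated odds hypothesis, and Limitations names multivariable regression as part of the answer to the difference between caregiver and patient views. An inflated odds ratio for fluctuation intensity could mislead the later work on recall periods that the Discussion hopes to inform.

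**Working it through.** **The plan's own figure.** No significance level, power, effect size or event rate is given, so 50 cannot be derived. The only numerical link is 20 fluctuating patients out of 50, which is 40%. The binomial probability of reaching at least 20 is 0.55 if the true share is 40%, 0.80 at 45% and 0.94 at 50%. This concerns how many patients fluctuate; it says nothing about the regression.

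**Ceiling on events.** I assume one adherence answer per dyad, taken from the day-14 interview. The smaller class is then at most 50/2 = 25, and 15 if non-adherence is 30%.

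**Parameter count.** Three intensity levels use 2 parameters. The text names both socio-demographic and clinical variables, so the smallest reading that fits it is 2 + 1 + 1 = 4. If all eight baseline variables enter, each with one term, the count is 2 + 3 + 5 = 10.

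**Events per parameter** (smaller class / parameters):

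| Parameters | 25 events | 15 events |
|---|---|---|
| 4 | 6.25 | 3.75 |
| 6 | 4.2 | 2.5 |
| 10 | 2.5 | 1.5 |

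**Simulation.** The assumptions are mine, not the document's: n = 50; intensity classes equally likely; true odds ratio 3 for high versus low (log 1.10) and half that log effect for moderate versus low; independent covariates with log odds ratio 0.3 each; overall non-adherence 50% or 30%; 4,000 samples per row. Fits that did not converge were dropped (under 1% of maximum-likelihood fits at 50% non-adherence, 4 to 5% at 30%), which understates the instability. Bias is the mean estimated log odds ratio divided by log 3, minus 1, with a simulation error of 1 to 2 points.

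| Parameters | Non-adherence | ML bias | ML odds ratio, 5th–95th percentile | Firth bias | Firth odds ratio, 5th–95th percentile |
|---|---|---|---|---|---|
| 4 | 50% | +13% | 0.9–16 | +1% | 0.9–11 |
| 4 | 30% | +11% | 0.8–16 | +1% | 0.8–13 |
| 6 | 50% | +21% | 0.8–21 | +2% | 0.9–12 |
| 6 | 30% | +19% | 0.7–22 | +2% | 0.8–14 |
| 10 | 50% | +48% | 0.7–55 | +6% | 0.8–16 |
| 10 | 30% | +48% | 0.6–77 | +6% | 0.7–20 |

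Repeat runs with other random seeds put the maximum-likelihood bias at 10 to 15% for 4 parameters and 44 to 53% for 10, and the Firth bias at 10 parameters between 2 and 6%.

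**Precision.** Power to detect the true odds ratio of 3 by maximum likelihood is about 31% at 50% non-adherence and 20 to 23% at 30%, whatever the parameter count. Even with intensity alone (2 parameters) at 50% non-adherence, the bias is only about 8%, yet the median 95% confidence interval has an upper limit about 19 times its lower limit. With 10 parameters, power reaches about 51% at n = 100 and 83% at n = 200.

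**What 50 dyads do support.** For a simple proportion the 95% half-width is at most 1.96 × √(0.25/50) = 0.139, about 14 percentage points.

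**The case against.** The strongest reply is that the 10-parameter model is not in the document. The article speaks only of further variables, with no number and no statement that all eight enter. The choice may sit in an analysis plan that is not shown, and its absence is no defect. This stands: 10 is the upper end of a range, and a reader who infers that the plan fixes it, or that a 45% overstatement is certain, goes beyond the text. Classes of equal size are likewise my assumption, since no cut-points are given.

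It can also be said that unpenalised maximum likelihood is not named. That is literally so, but a plan for multiple logistic regression without qualification is ordinarily carried out that way, and the remedy is to say otherwise.

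A reader might further infer that 50 dyads cannot deliver objective (iii). The documents do not support that. The objective is to evaluate whether past fluctuations are considered, and caregivers are asked this directly on day 14; cross tables, descriptive statistics and thematic analysis also address it. The design is declared explorative. Nor does the sample-size section rest on the 20 fluctuating patients alone.

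What remains is independent of the missing list: no choice of covariates raises the ceiling of 25, and the smallest reading that fits the text still gives biased and very imprecise odds ratios.

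**Conclusion.** The point holds in a limited form. A logistic model with three-level intensity and covariates of both kinds, fitted in 50 dyads by ordinary maximum likelihood, has at most 2.5 to about 6 events per parameter. It overstates a true odds ratio of 3, on the log scale, by about 10 to 14% at 4 parameters and 45 to 48% at 10, with estimates anywhere from below 1 to about 16 or about 80. These sizes rest on the simulation assumptions and on 30 to 50% non-adherence; a rarer class would do worse. If only fluctuating patients are analysed and there are just 20 of them, the smaller class is at most 10, and about 82% of 10-parameter fits fail.

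What is not supported is the adjusted odds-ratio hypothesis as something 50 dyads can settle, together with a sample-size sentence that covers all aims without qualification. The descriptive and interview answer to objective (iii) is unaffected.

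**What to change.** In Quantitative data preparation and analyses:

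- Fit the adherence model with Firth's penalised likelihood, which is available in the planned software. In the simulations this brings the bias to roughly 6% or less even with 10 parameters.
- Enter intensity as one continuous score, the mean absolute daily change from the diary. The plan already summarises intensity as a mean change per day; absolute values stop better and worse days from cancelling. This saves one parameter and needs no cut-points, but assumes a linear effect on the log-odds scale. Its gain in precision was not isolated here.
- Name in advance a few patient covariates from the baseline list, and show the others in cross tables. How few is a judgement for the investigators.
- Report the model as exploratory, with confidence intervals.

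In Sample size, state that 50 dyads support descriptive estimation (at most about ±14 percentage points for a proportion) and only an imprecise exploratory regression.

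No new data are needed; only wording changes. The price is fewer adjusted variables and a less favourable sample-size statement. Penalisation does not create information: with 10 parameters at 50% non-adherence, power falls from about 31% to about 19%, because the overstated estimates are pulled back, and intervals stay wide.

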i. To assess the frequency and intensity of the health state fluctuation, caregivers document if patients' today's health is much (+2) or somewhat better today (+1), about the same (±0) today, or somewhat (−1) or much (−2) worse today compared to the day before. Also, a repeated administration of the EQ-5D-5L will also assess the health state fluctuation as a self- and proxy-rating at baseline (before starting the diary), seven days after starting the diary, and on the last day of the diary (day 14). The change in the EQ-5D-5L utilities, EQ-5D-5L level scores and level sum scores (LLS), and EQ-VAS scores from day 1 to day 7 and day 7 to day 14 can be used to assess the variability and reliability of each measure.ii. To assign health state fluctuations to specific health dimensions, we will use the health dimension of the diary and the assessment of EQ-5D-5L dimensions at baseline, seven, and 14 days. The caregiver will be instructed to document in the diary which dimensions could be assigned to the fluctuation of today's health state compared to the day before. We will use dimensions of the EQ-5D-5L and two other patient-reported outcomes measures (PROMs), the EQ Health and Wellbeing instrument (EQ-HWB) (22) and the dementia-specific Quality of Life–Alzheimer's Disease (QoL-AD) (23). The EQ-HWB has been designed as a standardized measure of aspects of health and well-being and has 25 items (24). In comparison, the QoL-AD is a widely used measure of the quality of life in dementia diseases that contains 13 items evaluating the domains of interpersonal relationships, financial difficulties, physical condition, memory, mood and overall health. Furthermore, caregivers could specify any other affected dimensions not listed in the diary. All dimensions are shown in Figure 2.iii. Caregivers will also be asked to document any health events that could have caused the health state fluctuations.iv. To evaluate the consideration of past health state fluctuations in the assessment of today's health, the EQ-5D-5L will be administered on day 14. Subsequently, the caregivers will be interviewed and asked whether or not recurrent health state fluctuations (if applicable) were considered in the assessment of health today using the EQ-5D-5L administered minutes before starting the interview. Furthermore, the caregiver will be asked to state what recall period would be more appropriate to assess HRQoL in people living with dementia more accurately.

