### Statistical analyses

#### Quantitative data preparation and analyses

Patient and caregiver characteristics will be demonstrated descriptively. Descriptive statistics will also describe health state fluctuations' occurrence, frequency, and intensity. The occurrence will be operationalized dichotomously: no fluctuations reported vs. at least one fluctuation reported. The frequency will be quantified as the number of fluctuations within 14 days. The intensity will be operationalized as follows: much worse or better = ±2; somewhat worse or better = ±1; about the same = ±0) of the reported health events. We will demonstrate the intensity of the health state fluctuations as a mean change per day with standard deviation.

Furthermore, we will use exploratory data analysis of the EQ-5D-5L data by reporting the number and percentage of patients reporting each level on each dimension of the EQ-5D-5L using simple descriptive statistics (26). The EQ-5D-5L profile and EQ-VAS scores will also be demonstrated using descriptive statistics. Also, change in EQ-5D-5L index, EQ-VAS and LLS will be demonstrated descriptively [mean value of change, Intra Class Correlation (ICC)] over the fluctuation intensity. Furthermore, cluster analyses will be used to identify frequent health events or a combination of events.

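### The hypothesis is about EQ-5D-5L variability, but the statistics named for it compare means, and no variability outcome is defined

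*Protocol article*

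**What the plan says.** All of this is in the protocol article, mostly under Quantitative data preparation and analyses.

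- **Hypothesis.** More frequent and more intense diary fluctuation "will cause higher variability of the EQ-5D-5L index between baseline and seven or 14 days later". The same sentence holds a second hypothesis, on the odds that past fluctuation was considered when rating health today.
- **Outcome for the association.** The diary measures are to be related to "the differences between the baseline, 7-day and 14-days follow-up EQ-5D-5L profile, health utility and EQ-VAS".
- **Tests.** The list is open: "we will use appropriate statistics such as cross tables with ANOVA", followed by t-tests and logistic regression. The only model with a named dependent variable is the one for adherence to the recall period.
- **Descriptive summary.** The "change in EQ-5D-5L index, EQ-VAS and LLS will be demonstrated descriptively", as "mean value of change, Intra Class Correlation (ICC)] over the fluctuation intensity".
- **Purpose of the change scores.** Under Outcome measures to assess health fluctuations, the changes over the two intervals "can be used to assess the variability and reliability of each measure".
- **Diary exposures.** Occurrence is any against none. For the count, "The frequency will be quantified as the number of fluctuations within 14 days". Intensity is a mean change per day with its standard deviation, from daily scores of −2 to +2, and it enters the regression as low, moderate or high.

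**The concern.** Fluctuation, as the Introduction describes it, is an alternation of better and worse days, and the diary scale is symmetric about zero. For a patient who swings widely, the EQ-5D-5L difference between two visits can fall either way. Averaged over such patients, the signed difference may be close to zero, as it is for stable patients. What separates the groups is the spread of the differences, and the hypothesis is about that spread. A t-test or ANOVA on signed differences tests whether the group means differ, which is another question.

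The diary side can cancel in the same way: if the mean change per day is taken over signed scores, ups and downs offset each other.

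At stake is the reading of a null result. A non-significant comparison of mean change could be reported as showing that fluctuation does not affect the EQ-5D-5L, when the comparison was hardly able to show it.

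**Working it through.** **Inputs from the article:** 50 dyads; three EQ-5D-5L ratings (baseline, day 7, day 14); a 14-day diary scored −2 to +2. No alpha, power, effect size or SD is stated and n = 50 has no formula behind it, so there is no figure to reproduce.

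**Assumptions:** two-sided alpha 0.05; normally distributed change; true mean change zero in every group; SD of change r times larger in high than in low fluctuators. Group sizes are assumed, because no cut-offs for intensity are given.

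**1. Why the mean carries no information here.** If change D is normal with mean 0 and SD σ, then E(D) = 0 for every σ, but E|D| = σ√(2/π) = 0.798σ. With σ = 1 in the low group, mean signed change is 0 in both groups, while mean absolute change is 0.80 against 1.20, 1.60 and 1.99 at r = 1.5, 2 and 2.5.

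**2. Two groups, 20,000 simulated studies per row, share rejecting:**

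| Groups (low/high) | r | t-test, signed change | Welch test, absolute change | Brown-Forsythe |
|---|---|---|---|---|
| 25/25 | 1.5 | 5% | 42–43% | 38% |
| 25/25 | 2 | 5% | 85% | 82% |
| 25/25 | 2.5 | 5–6% | 98% | 97% |
| 17/17 | 1.5 | 5% | 29% | 24% |
| 17/17 | 2 | 5–6% | 67% | 60% |

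With 33 low and 17 high fluctuators at r = 2, the ordinary t-test on signed change rejects in 11%. That is size distortion from unequal variances; the unequal-variance version returns to 5%.

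**3. Three intensity groups (17/17/16), 4,000 simulated studies per row.** Baseline-to-day-14 change for the first two tests; low-group within-person SD 0.5, between-person SD 1; within-person SD ratio low:moderate:high as shown.

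| Ratio | ANOVA, signed change | ANOVA, absolute change | ANOVA, within-person SD of three ratings |
|---|---|---|---|
| 1:1.25:1.5 | 5.3% | 23.2% | 45.1% |
| 1:1.5:2 | 6.7% | 55.5% | 90.7% |
| 1:2:3 | 5.8% | 91.3% | about 100% |

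Using all three ratings through the within-person SD gains a good deal over one absolute change.

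**4. What the planned ICC would show.** ICC = between-person variance / (between-person variance + within-person variance). With between-person variance 1 and within-person SD 0.5, 0.75 and 1.0, this gives 1/1.25 = 0.80, 1/1.5625 = 0.64 and 1/2 = 0.50. The simulated averages are 0.78, 0.62 and 0.48. The effect is visible. But the same formula moves if the between-person variance differs across strata, and no comparison of ICCs is planned.

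**5. Diary side, illustrative symmetric score distributions.** For stable, moderate and highly fluctuating patients the signed daily mean is about 0 in all three. The mean absolute score is 0.10, 0.60 and 1.30, and the SD across days is 0.27, 0.87 and 1.44.

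**6. Time windows.** The frequency count spans 14 days, while EQ-5D change is taken "from day 1 to day 7 and day 7 to day 14 can be used". With equal weekly variances and week-to-week correlation ρ, the 14-day total correlates √((1+ρ)/2) with its own week: √0.5 = 0.71 at ρ = 0 and √0.8 = 0.89 at ρ = 0.6 (ρ assumed).

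**The case against.** The strongest reply is that the article nowhere says the differences are signed. It gives assessing variability as a use of the change scores, pairs better and worse at each intensity score, and grades intensity from low to high, which suggests magnitude. A t-test on absolute differences would be close to what is proposed here. The list of tests is open, the article condenses a fuller plan, and the analysis plan is not shown. This stands to the extent that the fault is an undefined variability outcome and not a fixed wrong one. It does not remove the point: the article names a hypothesis, an outcome and tests, and on their plain reading, with mean change as the stated summary, they do not fit together.

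A reader might go further and infer that an effect on variability would be missed altogether. The documents do not support that. The ICC by intensity would partly show it, and change running mainly in one direction would show in signed means.

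Nor is everything set against a 14-day total. Only frequency is such a count, it matches the baseline-to-day-14 change exactly, and for the day-7 change it can be defended as a measure of a patient's general tendency to fluctuate.

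It would also be too much to call this the study's main hypothesis. The study is explorative, no power is planned, no listed objective is to test this association, and the companion hypothesis on recall adherence has a fitting logistic model.

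Finally, the better outcome is no cure for a small sample: at r = 1.5, absolute change rejects in only 29–43% with equal groups.

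**Conclusion.** The point holds as a mismatch between a hypothesis on variability and named statistics that compare means. With signed differences, balanced ups and downs and equal groups, those tests stay at about 5% whatever the effect on variability. A test on absolute change rejects in about 42%, 85% and 98% at SD ratios of 1.5, 2 and 2.5 with 25 against 25. These figures rest on the signed reading, zero mean change, normality, and assumed group sizes and SD ratios, none of which the article gives. The mismatch of diary and EQ-5D windows is a secondary matter. Severity is moderate: the study is explorative and the descriptive ICC gives partial cover, but the repair costs almost nothing and prevents a misleading null result.

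**What to change.** In Quantitative data preparation and analyses:

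1. Name the outcome for the variability hypothesis: the absolute EQ-5D-5L change per interval, or the within-person SD over the three ratings. The second used the data better in the check above.
2. State that diary intensity for this analysis is the mean absolute daily change, so that better and worse days do not cancel.
3. Relate the two by regression. If groups are compared, use an unequal-variance test on the absolute change or a Brown-Forsythe test on the change itself.
4. Keep signed mean change as a description of drift and the ICC by intensity as a descriptive complement, reported with the between- and within-person variances.
5. As a secondary refinement, relate diary days 1–7 to the baseline-to-day-7 change and days 8–14 to the day-7-to-day-14 change, and keep the 14-day count for the baseline-to-day-14 change.

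The cost is analysis wording only. No new data, visits or participants are needed.
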